### Outcomes

#### Primary outcome: satisfaction with the breast/s and breast-specific quality of life

BREAST-Q reconstruction module (version 1) is a validated disease-specific patient-reported instrument that measures outcomes after breast reconstruction, breast-related quality of life and patient satisfaction.^25^,^27^ The following domains will be analysed: satisfaction with breast/s, satisfaction with outcome, psychosocial well-being chest, sexual well-being, physical well-being chest and satisfaction with information. The patient rates all items in the domains on 3-point, 4-point and 5-point Likert scales. A raw score that is converted to a score of 0–100, is calculated for each domain. A higher score indicates greater satisfaction or a better quality of life. Normative data have been described for a Swedish population^36^ and it will be used for reference values. A further validation of the Swedish version is ongoing in our department.

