### Study objectives

The main overall purpose of breast reconstruction is to increase the woman’s quality of life, both physically and psychosocially. Therefore, the primary objective/outcome is to compare the two methods regarding patient-reported breast-specific quality of life and satisfaction. These measures are also part of the core outcome set for breast reconstruction developed by patients and professionals.^21^

The secondary objectives are to compare the two methods regarding complications, unplanned operations, corrections, cost-effectiveness and factors that might affect the primary outcome. Other secondary objectives are to improve the evidence for trial decision-making in breast reconstruction to improve the methodological design and process of future studies by means of a study within a trial (SWAT).^22^

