#### Sample size

The study is s a superiority trial based on the BREAST-Q domain *Satisfaction with the breast/s*.^25^,^27^ The clinically meaningful difference in BREAST-Q was set to 10 points. There are no anchor-based minimal important differences (MIDs) published for BREAST-Q, but the distribution-based MID is 4 for satisfaction with the breast/s.^28^ The SD was set to 18, as calculated according to US norms.^29^ If power is set to 0.80 and alpha to 0.05, the case-to-control ratio is 1, and a 20% dropout rate is expected, 62 patients are needed in each group (https://riskcalc.org/samplesize/). In the randomised cohort, 124 participants will be randomised 1:1. In the preference cohort, patients will be included until 62 participants have selected the least popular alternative (figure 3). This will result in an overall trial cohort with a minimum of 124 participants in each arm and enough participants in the subgroups *randomised* and *patient preference* to allow for analyses of differences.

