### Statistical methods

A detailed statistical analysis plan will be drafted early in the trial and finalised before primary outcome analysis. All analysis will be performed on an intention-to-treat basis and per-protocol analysis as sensitivity analysis. Descriptive data will be given as appropriate according to type of data and if it is skewed or not. This will also form the basis for statistical tests chosen to compare groups. Sensitivity analysis will be done were missing data in predictors will be handled by multiple imputation methods.^50^ Regression analysis preceded by collinearity check of potential predictors and performed to allow for correction for possible confounders. Residuals for each regression analysis will be checked for the assumptions of normal distribution and constant deviation along the predicted values. Subgroup analyses will be performed for the randomised and the preference cohort and for timing of reconstruction (immediate/delayed reconstruction) and for patients who unexpectedly will require radiotherapy. The statistical analysis will adhere to the Setting Intenartional Standards in Analysing Patient-Reported Outcomes and Quality of Life Endpoints in Cancer Clinical Trials (SISOQOL) framework.^51^ All tests will be two tailed and a p value of ≤0.05 will be considered to indicate a statistical significance.

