### Adherence

Trial participants will be given their scheduled follow-up appointment at hospital discharge, with the following scheduled by post. A reminder text message will be sent prior to the appointments to improve adherence. Patient-reported outcome measure instruments will be given to the patient when they are allocated to treatment and then sent by mail at the subsequent timepoints. Two reminders will be sent to the patients if a questionnaire reply is not received by the hospital. Questionnaires will be given to the participants at allocation and then sent by mail, with up to two reminders, at the remaining timepoints, with reminders to ensure continued participation.

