### Retention

Any trial participant lost to follow-up will be contacted to complete the 3, 12, 36 and 60 months follow-up. The trialists will make every reasonable effort to follow participants for the entire study period. If available, a reason for withdrawal will be documented.

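### The trial is sized on one BREAST-Q domain, but the primary outcome is written as six unranked domains with no primary follow-up time in the text

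*Protocol article*

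**What the plan says.** The protocol article describes the primary outcome in different ways in different sections.

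- **Sample size** calls the study a "superiority trial based on the BREAST-Q domain" satisfaction with the breast/s. It sets a 10-point difference, SD 18, power 0.80, alpha 0.05 and 20% dropout, and arrives at 62 per group.
- **Study objectives** is broader: "the primary objective/outcome is to compare the two methods regarding patient-reported breast-specific quality of life and satisfaction".
- **Primary outcome** names both constructs in its heading and lists six domains for analysis: "The following domains will be analysed: satisfaction with breast/s, satisfaction with outcome, psychosocial well-being chest, sexual well-being", and then physical well-being of the chest and satisfaction with information. They are not ranked. The secondary outcomes start in the next section, so all six sit on the primary side.
- **Statistical methods** gives one threshold for everything: "All tests will be two tailed and a p value of ≤0.05 will be considered to indicate a statistical significance". It also says that a detailed statistical analysis plan (SAP) will be finalised before the primary outcome analysis.
- **Adherence** covers data collection: "Questionnaires will be given to the participants at allocation and then sent by mail, with up to two reminders, at the remaining timepoints". **Retention** says that participants lost to follow-up will be "contacted to complete the 3, 12, 36 and 60 months follow-up". The text singles out none of these times as primary.

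**The concern.** The sample size calculation describes one comparison of one variable. The objectives and outcome sections describe a primary outcome made of several variables, and no section fixes when it is read. The stated alpha and power therefore belong to one test, while the protocol leaves room for more than one test to be reported as the primary result.

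This matters because the article expects the trial to show which method is superior and to inform guidelines and budgets. The trial is not blinded and outcome data begin to arrive early. A choice of domain or time made only at the end would therefore be open to question, even if it was made in good faith. Which variable and which time decide the trial is normally fixed in the protocol. Here the protocol's own sections disagree about the variable.

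**Working it through.** **1. Reproduce the planned size.** Inputs from the Sample size section: difference 10, SD 18, two-sided alpha 0.05, power 0.80, dropout 20%.

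- n per group = 2 × [18 × (1.960 + 0.842) / 10]² = 50.9, so 51 evaluable.
- 51 × 1.20 = 61.2, so 62. This is the stated figure.
- Dividing instead, 51 / 0.80 = 63.75, so 64. The two-patient gap is immaterial here.
- With 62 × 0.80 = 49.6 evaluable per group, power is 0.79.

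The stated 62 per group is sound for one test of one domain at one time.

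**2. Error rate if several tests can each give the primary result.** Assume no true difference and each test at two-sided 0.05. Under independence, the chance of at least one significant result in k tests is 1 − 0.95^k. The correlated figures come from 200,000 multivariate normal draws with equal correlations. The documents give no correlations, so those used are assumptions.

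| Reading | k | Independent | Correlation assumed | Result |
|---|---|---|---|---|
| Six domains, one time | 6 | 1 − 0.95^6 = 26.5% | 0.3 / 0.5 / 0.7 between domains | about 24% / 21% / 16% |
| Sizing domain only, any of four follow-ups | 4 | 1 − 0.95^4 = 18.5% | 0.5 / 0.7 between times | about 16% / 13% |

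**3. Cost of keeping all six domains primary.** At one time with a Bonferroni split, alpha = 0.05 / 6 = 0.00833.

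- Evaluable patients needed: 79 per group. After dropout, 79 / 0.80 = 98.75, so 99 per group.
- With the planned 62 per group (49.6 evaluable), power for a 10-point difference is 0.55 per domain.

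The planned size fits one primary test and does not fit six.

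**The case against.** The best defence is that the Sample size section ties the superiority framework itself, and not only the arithmetic, to satisfaction with the breast/s. The first research hypothesis is also about satisfaction with the reconstructed breast, and that domain comes first in the outcome list. The outcome section says only that the six domains will be analysed and does not call each a co-primary test. The SAP is not shown. It may set a hierarchy, a multiplicity rule and an analysis time, and a general 0.05 threshold does not rule these out.

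Much of this stands. The lack of a multiplicity method would not be a finding on its own, and a careful reader may well take the sizing domain as the intended key one. But the objectives and outcome sections do not say so, and what they do say is broader. Even on the favourable reading, the text names no primary time.

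Three stronger readings are tempting but not supported:

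- **Twenty-four primary tests.** A reader might multiply six domains by four follow-ups and obtain 1 − 0.95^24 = 71% under independence, or about 38–60% with assumed correlations of 0.7–0.3 between domains and 0.7–0.5 between times. The text nowhere says that every domain is tested at every time. The four times come from a paragraph on retention, and the timeline figure is not shown. This is an upper reading only.
- **The 3-month rating falls at the expander exchange.** The exchange is timed from the initial operation, but the retention paragraph does not say where its 3 months start. Elsewhere the article counts both from allocation (economic evaluation) and from reconstruction (interviews). Nothing suggests that 3 months is meant as the primary time.
- **Satisfaction with information cannot reflect the method.** Counselling is standardised, but this does not show that later ratings are unaffected by the operation or its result.

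**Conclusion.** The point holds as a conflict within the protocol. One domain carries the sample size and the superiority framework, while the objectives and outcome sections present a wider, unranked primary outcome, and the text gives no primary time.

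If the wording were followed literally, the chance of a false-positive primary result would exceed the nominal 5%. It would be about 16–27% with six primary domains at one time, and about 13–19% with only the sizing domain but a free choice among four follow-ups. The upper end of each range assumes independence, and the lower end assumes a correlation of 0.7.

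A reader might infer that the trial has no control of its error rate. The documents do not support that, because the SAP is unseen and may supply it. The sample size is not wrong for the single test it describes.

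**What to change.** State in the Study objectives and Primary outcome sections that BREAST-Q satisfaction with the breast/s, at one pre-specified follow-up time with its starting point given (allocation or reconstruction), is the sole primary endpoint, tested at two-sided 0.05. Make the other five domains and the other times secondary. Handle them by a fixed testing order, by Holm correction, or as estimates with intervals and no confirmatory claims. Carry the same wording into the registry entry and the SAP, and settle it before any outcome data are examined.

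This needs wording only. It requires no new data and keeps the planned 62 per group. The price is that fewer results can be called confirmatory. If the sponsor prefers to keep all six domains primary, the protocol needs a stated procedure that controls alpha and a larger sample, about 99 per group under Bonferroni at one time.

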#### Secondary outcomes

All adverse events are classified according to the Clavien-Dindo Classification (CDC) of surgical complications and Comprehensive Complication Index (CCI) scores,^37^ as well as specific complications. CDC and CCI are currently being validated for breast reconstruction in our department. All participating surgeons will be given a list of study-specific definitions of *complications and corrections/revisions. Satisfaction with the donor-site* will be measured with BREAST-Q donor site domains, expectations with BREAST-Q expectations domain,^38 39^
*symptoms of depression and anxiety* with Hospital Anxiety and Depression Scale (HADS),^40 41^
*body image* with the Appearance Schemas Inventory-revised (ASI-R)^42^and the Multidimensional Body-Self Relation Questionnaire (MBSRQ),^43^
*generic quality of life* with EuroQoL-5 dimensions (EQ-5D-3L),^44^ and the *patient’s goals with the reconstruction* will be documented using PEGASUS.^20^

The BREAST-Q donor site module has two domains (satisfaction with abdomen and physical well-being: abdomen) and the expectations module has six domains (support from medical staff, pain: postop, coping, appearance: clothes, sensation: breasts, and function: abdomen) and they are scored as described under ‘primary outcomes’. HADS^41^ measures symptoms of anxiety and depression in somatically ill patients on a Likert scale. For both domains, scores of less than 7 indicate non-cases, whereas scores of 8–10 indicate possible cases and scores of >10 indicate probable cases.^40 45 46^ The ASI-R measures body image investment, how important the individual believes their physical appearance is for her/his own self-worth. It is measured on Likert scales and has two domains: self-evaluative salience and motivational salience. The scores for the two domains are calculated as the mean of the items for each subscale. The total ASI-R score is the mean of all 20 items. A higher score indicates greater body image investment.^47^ The MBSRQ measures appearance-related aspects of body image on Likert scales and has four domains: appearance evaluation, appearance orientation, body areas satisfaction and overweight preoccupation.^43^ EQ-5D-3L has five dimensions: mobility, self-care, usual activities, pain/discomfort and anxiety/depression. The patient rates his/her health on a three-level Likert scale and a score is calculated, where 1 indicates ‘perfect health’ and 0 ‘death’. EQ-5D-3L The instrument also comprises a visual analogue scale where the patient marks his/her current health state, from 0 (‘worst imaginable’) to 100 (‘best imaginable’).^44 48^ The PEGASUS instrument is described under ‘Uniform preoperative counselling’.

### Study within a trial

The RPPT design will be assessed quantitatively using a SWAT.^22^ This considers the rate of patients fulfilling the criteria and agreeing to participate in the study, the time it takes to recruit the target number in each group, the rate of patients who accept randomisation and differences between the randomisation and preference cohort regarding demographic factors as well as preoperative satisfaction with breasts, expectations, body image, symptoms of depression and anxiety, and generic quality of life. To obtain insights into attitudes towards and experiences of the study process, semistructured interviews will be conducted concerning issues such as how the process can be ameliorated to increase recruitment, retention and follow-up rates of questionnaires, and how the participation information leaflet should be improved to maximise recruitment. Trial participants, participating surgeons and research nurses will be interviewed. Embedded qualitative studies will be used to investigate the participants’ thoughts, attitudes and experiences regarding:

*The choice of breast reconstruction and the choice of reconstructive method*. Participants will be recruited from the preference cohort. Longitudinal—the same participants will be interviewed at allocation and 12 months after the reconstruction.*What makes a participant very satisfied or very dissatisfied*. Participants will be recruited from both cohorts among women who scored high/low, compared with the mean, on BREAST-Q outcome and satisfaction with breast/s.*SWAT*^22^*: How the participant experienced the trial process, how it can be ameliorated to increase recruitment, retention and follow-up rates of questionnaires and how the participation information leaflet should be designed/written to maximise recruitment*. Different participants from both cohorts are interviewed at allocation, 3 and 12 months to explore if there are different themes at different time points.

Qualitative approaches and research paradigms will be chosen based on the type of question studied. Interview guides are given as online supplemental appendix 3. A purposive criterion-sampling technique will be used at the time points described in figure 4. Interviews will follow semistructured interview guides designed for each research question. Participants will be recruited until saturation has been achieved.

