Randomised controlled trials (RCT) are generally thought to provide the most solid scientific evidence for treatment effects. However, there are barriers to conducting RCTs in breast reconstruction, making both recruitment and achieving unbiased and generalisable results a challenge.^9 10^ First, an RCT requires that there is solid uncertainty about which method achieves the best results. In the case of breast reconstruction, the operating surgeon must not prefer one method to another (*theoretical equipoise*)^11^ as this could result in both biased recruitment as well as biased outcomes if the included patients receive biased preoperative and postoperative information.^9^ The patient must also not have preformed ideas and clear preferences regarding the different methods (*principle of indifference*)^11^ based on, for example, other patients, patient organisations, and the media, as this also affects the recruitment and the results. Patients’ preferences can affect the external validity if a standard treatment, for example, implant-based breast reconstruction in non-irradiated patients,^12^ is compared with an alternative treatment, for example, autologous reconstruction, as only patients who prefer autologous reconstruction are likely to accept randomisation. Patients’ preferences could also reduce internal validity as randomisation to the (non-) preferred strategy could affect both adherence to the protocol (*reluctant acquiescence phenomenon*)^13^ and outcome. All these factors would lead to results that are not generalisable to the clinical population. This risk of bias and low internal and external validity illustrates why an RCT can be an inappropriate study design when comparing different categories of breast reconstruction.

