### Trial design

GoBreast II is a partially RPPT with a superiority framework. Participants who accept randomisation will be allocated to one of the two methods. Participants who do not accept randomisation will be operated with their preferred method. Thus, the study has two cohorts: one randomised and one patient preference (figure 1). The trial is a single-centre study conducted at a university hospital in Sweden. It has embedded qualitative and health economic research questions.

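### The baseline comparison in the study within a trial treats the preference cohort as one group, so it can dilute differences from randomised women and cannot show which choosers differ

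*Protocol article*

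**What the plan says.** The section 'Study within a trial' lists what the SWAT will use to assess the partially randomised design. Beside recruitment and acceptance rates it names "differences between the randomisation and preference cohort regarding demographic factors". The list goes on to baseline breast satisfaction, expectations and body image, and then symptoms of depression and anxiety and generic quality of life. The groups are the two cohorts.

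'Trial design' defines them: "the study has two cohorts: one randomised and one patient preference". It adds that "Participants who do not accept randomisation will be operated with their preferred method", so women with opposite choices share one cohort. 'Sample size' fixes the numbers. "In the randomised cohort, 124 participants will be randomised 1:1", and "In the preference cohort, patients will be included until 62 participants have selected the least popular alternative". The number choosing the more popular method is open. The same section adds the cohorts together: "This will result in an overall trial cohort with a minimum of 124 participants in each arm".

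'Statistical methods' lists subgroups by cohort, by immediate or delayed timing, and by unexpected radiotherapy, but not by chosen method. The Discussion section on the RPPT design says the SWATs will show how many women prefer each option. No section plans a comparison of baseline characteristics by chosen method.

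**The concern.** The preference cohort's mean on age, expectations, body image or anxiety is an average over two self-selected groups, weighted by how popular each method turns out to be. These groups may sit at different distances from the randomised women, or on opposite sides of them. A cohort-level comparison then has three weaknesses:

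- A difference confined to one chooser group is diluted by the other.
- Two differences of opposite sign offset each other, fully so if the mix matches.
- Whatever the result, it does not say which choosers differ from randomised women, or by how much the chooser groups differ from each other.

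Two uses are affected. One is describing who accepts randomisation, which is part of what the SWAT is for. The other is interpreting the overall cohort. There the DIEP arm gains DIEP-choosers and the implant arm gains implant-choosers, while the randomised women are balanced between arms in expectation. Baseline imbalance between the overall arms therefore comes, in expectation, from the choosers, and the stated comparison does not estimate the gap between the two chooser groups.

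**Working it through.** **The plan's own figure.** The SWAT comparison has no sample size of its own; its group sizes come from the main calculation. For a 10-point difference, SD 18, two-sided alpha 0.05 and power 0.80, the normal formula gives 51 per group. Then 51 × 1.2 = 61.2, so 62, as stated. (Dividing by 0.8 instead gives 63.75, so 64; that does not matter here.) This gives 124 randomised women and at least 62 per choice.

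**Inputs.** From the protocol: 124 randomised, 62 in the less popular choice, two-sided tests at 0.05. Assumed, because the protocol gives none of them: the size of the baseline shifts, the number choosing the more popular method, within-group SD of 1, and complete baseline data.

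**Formulas.** Let nD and nI be the numbers of DIEP- and implant-choosers, N = nD + nI, p = nD/N, and dD and dI their shifts from the randomised women in SD units.

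- Cohort difference: m = p·dD + (1 − p)·dI
- Preference-cohort variance: v = 1 + p·dD² + (1 − p)·dI² − m²
- Standard error: √(1/124 + v/N)
- Direct contrast, implant-choosers versus randomised: standard error √(1/124 + 1/nI)
- Power: Φ(|difference|/SE − 1.96) + Φ(−|difference|/SE − 1.96)

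**Case A: only implant-choosers differ (dD = 0, dI = −0.6).** Worked at 62/62: m = 0.5 × (−0.6) = −0.30; v = 1 + 0.18 − 0.09 = 1.09; SE = √(1/124 + 1.09/124) = 0.130; ratio 2.31; power 64%.

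| DIEP/implant choosers | Cohort difference (SD) | Power, cohort comparison | Power, implant-choosers vs randomised |
|---|---|---|---|
| 248/62 | −0.12 | 20% | 97% |
| 145/62 | −0.18 | 35% (0.345) | 97% |
| 62/62 | −0.30 | 64% | 97% |
| 62/145 | −0.42 | 95% | >99% |
| 62/248 | −0.48 | 99% | >99% |

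The same true difference shows up as anything from 0.12 to 0.48 SD, depending only on popularity.

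**Case B: opposite shifts (dD = +0.5, dI = −0.5).** At 62/62, m = 0 and the rejection rate is 5%, although the chooser groups differ by 1 SD (power above 99%) and each differs from the randomised women with power of about 90%. With one method more popular, the cohort comparison rejects in 40% (145 against 62) or 79% (248 against 62) of trials. Full cancellation is thus a special case and partial offsetting the general one.

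**Link to the overall cohort.** At 62/62 each overall arm is half randomised and half choosers, so the expected baseline gap between arms is 0.5 × (dD − dI): 0.5 × 0.6 = 0.3 SD in case A and 0.5 × 1.0 = 0.5 SD in case B. In case B the cohort comparison has expectation zero.

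**The case against.** Several points against the concern are sound.

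- *Accepters versus decliners is a legitimate question* for assessing this design. That stands, and is why the cohort comparison should stay.
- *Cancellation needs opposite signs and a matching mix*, and the protocol gives evidence of neither. That stands. If implants are the popular choice, which is plausible because 'Study setting' says they are the main current offer to non-irradiated women, the cohort comparison performs well in case A (95% to 99%).
- *A reader might infer that a null result would be taken as licence to pool the cohorts.* The protocol does not say so. The overall cohort follows from the recruitment rule and is not conditional on any SWAT result, and 'Statistical methods' plans regression to correct for possible confounders.
- *A reader might also infer that the protocol expects its own randomised women to resemble DIEP-choosers*, because the background says that "only patients who prefer autologous reconstruction are likely to accept randomisation". That sentence describes a conventional randomised trial of a standard against an alternative treatment. Here a woman who wants a DIEP-flap can choose it without being randomised.
- *A condensed article may leave the split by choice to the analysis plan.* This stands in part: nothing in the text rules the split out. But the text does name the groups to be compared, and that contrast cannot separate the two kinds of chooser. Counts of preferences and interviews about the choice do not supply the missing baseline contrast.

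**Conclusion.** The point holds as a limited, cheaply remedied weakness in a stated contrast. Two things follow from the design alone: the preference cohort mixes both choosers in an uncontrolled ratio, and a cohort-level comparison cannot locate a difference in either group or measure the gap between them. The size rests on assumed shifts. For a 0.6 SD difference confined to implant-choosers, detection by the cohort comparison ranges from 20% to 99% over the mixes 248/62 to 62/248, against 97% or more for the direct contrast. It would be too strong to say that differences will cancel, that the cohort comparison is useless, or that the trial will wrongly justify pooling. The primary analysis and the sample size are not affected.

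**What to change.** In 'Study within a trial', keep the comparison of the two cohorts and add a comparison of three groups: randomised, chose DIEP-flap, chose implant. For each listed baseline variable, report standardised differences with 95% confidence intervals for all three pairs. State that these will be used when describing who accepts randomisation and when interpreting the overall cohort.

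This is a change of wording and analysis only, with no extra participants or data. The cost is three further contrasts per variable, with groups as small as 62. In the smaller groups the intervals are wider, so the emphasis should be on estimates rather than on significance tests.
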